### Detailed descriptions of treatments A and B

Treatment A already existed before the start of the study. Treatment B is based on treatment A, but includes a shorter inpatient period in the first half year to reduce the burden for parents and children. This expands the opportunity for implementation of the learned behavior at home. Treatment B also focuses more on involvement of the parents from the beginning.

The focus of both treatments is on knowledge and skills and implementation. In both treatments the same topics are covered during the educational sessions, but the form in which the education is given is slightly different (guidance by a psychologist, dietician or exercise therapist in treatment A and by group coaches in treatment B).

Both treatment A and B are divided into 4 phases: 1. assessment/knowledge acquisition phase (week 1-6/1-8), 2. Knowledge acquisition and skills building phase (week 7-18/9-18), 3. Implementation phase (week 19-26) and 4. Maintenance phase (27-52).

#### Phase 1 (weeks 1-6 for treatment A, weeks 1-8 for treatment B)

During the first phase extensive physical and psychosocial examinations are carried out. The children are medically examined and they have several individual appointments with among others the dietician and psychologist, both with and without their parents, to assess what the problem areas are for each child. During this period the children receive schooling at a study centre at Heideheuvel, except for the primary school children. They go to primary schools in the neighborhood where the teachers can monitor dietary habits of the children. A very important secondary goal in this phase is also the group formation.

#### Phase 2 (weeks 7-18 for treatment A, weeks 9-18 for treatment B)

In the second phase, there are weekly (group A) or biweekly (group B after the inpatient period) educational group sessions for the children with a psychologist covering different topics, such as dealing with emotions, self confidence and self image. During this period, the children of treatment A go to a school in the vicinity of Heideheuvel. Children of treatment B continue to receive schooling at a study centre at Heideheuvel during the inpatient period and the biweekly return visits, when they are home they go back to the school in their own neighborhood.

#### Phase 3 (weeks 19-26 for treatment A as well as for treatment B)

In the third phase, the knowledge acquired in the previous phases is put into practice. In weeks 19 and 20 the children of group A have the last sessions of the weekly education program supervised by a psychologist and group coach. The children of group B will have their last session in the last biweekly return visit. From week 20 on in group A, one weekly visit to a movement therapist can be exchanged for a visit to a sports centre in the vicinity of the clinic, if the children like to perform sports not possible at the clinic. The children of group B continue to do exercise during their biweekly return visit. During phase 3 the children in treatment A go to a school in the vicinity of Heideheuvel Children of treatment B continue to receive schooling at a study centre at Heideheuvel when they are there for their biweekly return visit, when they are home they go back to the school in their own neighborhood. Around week 22 the children in treatment A return to their families once for a maximum of 1 week. This is to practice the learned skills at home during a normal week and see which problems are encountered in their home environment. After this family leave the encountered problems are discussed and if necessary plans are adjusted before the children are going back home again.

#### Phase 4 (weeks 27-52 for treatment A as well as for treatment B)

In the fourth phase, the maintenance phase, the children live at home again and go to their own school. During this period, which is aimed at preserving the acquired skills and maintaining the new body weight, there are monthly 2-day return visits for the children. During the second day of the return visits the parents also take part in the treatment. Each return visit a different topic related to the treatment is being discussed with the children in sessions both with and without the parents attending. The topics discussed are: autonomy, the family, dealing with emotions, my body, self confidence and self image. The topics also help to look ahead and plan how to tackle possible problems in the future. During these return visits also problems encountered at home are discussed and used as educational examples.

Table 1 describes for both treatments in detail the number of appointments the children have with different professionals of the multidisciplinary team in different phases of the treatment. In addition to the contacts described in the table, two group coaches are always present during the day to provide ongoing learning and education. They can support the children in the learned behavior and observe the children and discuss possible difficulties. During the night there is always supervision of a night nurse. For more information on the different disciplines involved see Table 2.

**Table 1 T1:** Details of treatment programs A and B in respect to visits to different health care professionals and treatment activities

	Treatment A				Treatment B			
**Disciplines/treatment parts**	**Phase 1 (weeks 1-6)**	**Phase 2 (weeks 7-18)**	**Phase 3 (weeks 19-26)**	**Phase 4 (weeks 26-52)***	**Phase 1 (weeks 1-8)**	**Phase 2 (weeks 10, 12, 14, 16, 18), n = per visit**	**Phase 3 (weeks 20, 22, 24, 26), n = per visit**	**Phase 4 (weeks 26-52)**

**Exercise therapist**	4G	4G	3G	2G	3G	2G	2G	2G
**Cesar therapist**	1G	1G	1G		1G (from week 3 on)	-	Once this phase G	
**Dietician**	1I, 1G	1I, 1G	1I, 1G	Once this phase	Twice I in first 2 weeks	-	-	Once this phase
**Pediatrician**	Every other week 1I	Every other week 1I	Every other week 1I	-	Every other week 1I	-	Once this phase I	-
**Psychologist**	2I this phase	Once this phase I 1G education	1G education	-	2I this phase	Once (children and parents) this phase G	Once this phase I	-
**Nurse**	Twice this phase I	Twice this phase I	-	-	-	-	-	-
**Laboratory**	Once I this phase	-	Once I this phase	Once I this phase	Once I this phase	-	Once I this phase	Once I this phase
**Social worker (parents)**	1G, 2I this phase	1G	1G	1G	1G	1G	1G	1G
**Parents course (parents)**	Twice this phase G	3 times this phase G	Once this phase G	-	8 times this phase G	Twice this phase G	-	-
**TTV**	-	-	Once this phase I, max 1 week	-	-	-	-	-
**Education/group-activity children**	-	-	-	1G	2 to 4G	2 to 4G	2 to 4G	3G
**Education/group activity/training parents and children**	-	-	-	1G	1G	6 times this phase G	5 times this phase G	2G

G = group session

I = Individual session

**Table 2 T2:** Explanation of different disciplines and treatment parts

Disciplines/treatment parts	Explanation of disciplines/treatment parts
**Parents course (parents)**	A course of several meetings for the parents in which different topics related to the treatment are being discussed under supervision of the social worker, such as making choices or handling temptations.

**TTV**	Temporarily therapy leave. A period with a maximum of 1 week in which the children of treatment A go home during the inpatient period to practice learned behavior in a normal setting during weekdays.

**Education/group-activity children**	Several topics related to the treatment are being discussed with the children under supervision of the group coaches such as motivation, bullying and self image Activities with the children are supervised by the group coaches. This can be something active like sport games or something to put an educational topic into practice.

**Education/group activity/training parents and children**	The educational sessions for both children and the parents together are always supervised by the group coaches and a social worker. Several topics related to the treatment are being discussed and occasionally the pediatrician or psychologist or dietician visits the session to discuss a certain topic. Activities with the children and their parents supervised by the group coaches and social worker. This can be something active like sport games or something to put an educational topic into practice.

### Measurements

Primary outcome measure is (SDS) BMI. Secondary outcomes are quality of life and cardiovascular risk factors like blood pressure, bodily circumferences, serum lipids, glucose levels and insulin levels. Eating behavior and physical activity are also assessed. The EuroQoL (EQ-5D) is used to measure quality of life and to calculate Quality Adjusted Life Years (QALYs) over the follow-up period of 24 months. Measurements will be done at four points in time: at baseline (start of treatment) and after 6, 12 and 24 months.

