## Methods/Design

### Design

This study is designed as a randomized controlled clinical trial with three study arms. The cost-effectiveness of two intensive one-year treatments that vary in inpatient period length and usual care for severely obese children and adolescents will be evaluated. There is a one year follow-up after treatment. Participants who meet the inclusion criteria and consent to participate in the study will be randomized to one of the three study arms (described under 'interventions'). Because of the nature of the treatments evaluated in this study, parents and participants as well as professionals at Heideheuvel and in the usual care condition cannot be blinded to the type of intervention. A table of random numbers is used to randomize participants. At the beginning of the first year 40 (13-18 years) participants are randomized into: group A (10), group B (10) or group C (20). The participants in group C will be randomized into group A (10) or B (10) after one year of receiving usual care. This process is repeated for another 40 participants (8-13 years) after 6 months. At the end of the fourth year all 80 participants (40 in each inpatient treatment group) will have completed the program and 1 year of follow up (Figure 1). Data collection started in August 2009 and will continue until July 2013. The Medical Ethics committee (METc) of VU University Medical Centre approved the study design, protocol and informed consent procedures.

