A challenge of the study will be keeping the attrition rate to a minimum. The study population is expected to have a relatively low socioeconomic status (SES) and to present relatively many psychological problems and socially complicated family structures. This can interfere with adherence to the treatment program. The psychological characteristics of the patients and their parents will be described in a separate study. Another difficulty will be the recruitment of participants, because of the extended inpatient periods. Especially in the group of children aged 8-13, we expect problems with recruitment because an inpatient period of 2 or 6 months imposes a very heavy burden on families and children. Also, because recruitment is nationwide, part of the parents will have to travel quite a lot, since their active participation and frequent presence during treatment is required. This can lead to high work absenteeism for the parents or loss of vacation days which will also be measured.

For the calculation of %BF the adjusted equation by Kushner et al is used [20], since the original equation by Kushner et al is developed to calculate total body water and is therefore not applicable. We have chosen for this equation after careful consideration as there are more suitable equations to calculate %BF specifically developed for obese children and adolescents such as the equations of Lazzer et al [32] and Schaeffer et al[33]. However we are limited in our choice because only resistance (R) is recorded. Cost calculations will be based on actual resource use; therefore prospective data collection through cost diaries during 2 years is used. However, the risk of this type of data collection is drop out; the longer the participant are followed, the higher the chance of loss to follow up. Also, bias can be introduced with this type of data collection, since it is based on self reporting. People can forget to note absenteeism or visits to health care professionals, even with the use of the cost diaries. By prospectively collecting data we hope to get valid estimates of health care utilization.

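### Baseline EQ-5D is set at the start of treatment, after an open randomisation, so the first point of the QALY can be influenced by the allocation, and group C's baseline is ambiguous

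*Protocol article*

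**What the plan says.** All references are to the protocol article.

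- **Order of events (Design).** "Participants who meet the inclusion criteria and consent to participate in the study will be randomized to one of the three study arms". Families and professionals "cannot be blinded to the type of intervention".
- **Timing (Measurements).** The first of four assessments is taken "at baseline (start of treatment"; the others follow at 6, 12 and 24 months.
- **Examinations (Phase 1).** "During the first phase extensive physical and psychosocial examinations are carried out". That phase is weeks 1-6 of treatment A and weeks 1-8 of treatment B, and Table 1 puts the first laboratory test there too.
- **Allocation (Design).** "At the beginning of the first year 40 (13-18 years) participants are randomized into: group A (10), group B (10) or group C (20"). A year later, "The participants in group C will be randomized into group A (10) or B (10) after one year of receiving usual care". The same scheme is repeated for the 8-13 age cohort.
- **QALY (Quality of life).** EQ-5D has five dimensions, one of them anxiety/depression. Utilities come from the Dutch tariff, and health states are joined by straight lines.
- **Before randomisation (Participants).** The clinic's pediatricians screen for eligibility, which needs an SDS-BMI value. No other measurement is placed before randomisation.
- **Analysis (Statistical analyses).** Intention to treat; GEE with age, sex, time point and group; multiple imputation of missing cost and effect data in the economic evaluation.

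The article does not say when families are told their allocation.

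**The concern.** A baseline is comparable between arms by design only if the allocation cannot have affected it. Here the allocations are very different pieces of news for a family: six months of weekday inpatient stay, two months, or another year of usual care. A child or parent who already knows the result may answer a questionnaire on anxiety, depression and usual activities differently from one who does not.

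The measure most exposed is EQ-5D, and its baseline value enters the QALY directly. The QALY difference is the denominator of the cost-utility ratio, so a small shift can matter when the true difference is small. Imputation does not help, because the affected value is observed.

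Two further gaps follow from the same definition. A family that leaves between allocation and treatment start misses the only planned baseline EQ-5D. And for group C, whose participants first receive usual care and are then randomised again, the definition does not identify a single date.

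**Working it through.** The plan gives no figure on this point. Its sample size of 40 per group does not depend on when baseline is taken, so there is nothing to reproduce first.

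**1. Does baseline follow allocation?** A and B begin with different inpatient programs, so an allocated treatment cannot start before the draw. With baseline at the start of treatment and no blinding, the sequence for A and B is consent, draw, baseline. That families know the result by then is an inference, but a strong one, since an inpatient stay has to be arranged with the family.

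**2. Weight of the baseline utility.** Visits are at 0, 0.5, 1 and 2 years. Under linear interpolation each visit's weight is half the sum of its adjacent intervals:

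- baseline: 0.5/2 = 0.25
- 6 months: 0.5/2 + 0.5/2 = 0.50
- 12 months: 0.5/2 + 1/2 = 0.75
- 24 months: 1/2 = 0.50

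The sum is 2.00 years, as it should be. For a 12-month comparison with usual care the weights are 0.25, 0.50 and 0.25, so the baseline weight is the same.

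**3. Effect of a shift.** If knowledge of the allocation moves baseline utility by *d* between arms and has worn off by month 6, the unadjusted QALY difference moves by 0.25 × *d*. The article gives no value for *d*, so a range is assumed:

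| Assumed *d* | Shift in QALY difference |
|---|---|
| 0.02 | 0.0050 |
| 0.05 | 0.0125 |
| 0.10 | 0.0250 |

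The direction is unknown.

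**4. Would adjusting for baseline remove it?** Not reliably. If *b* is the within-arm slope of the QALY on baseline utility, the adjusted difference moves by (0.25 − *b*) × *d*. Baseline's own contribution to *b* is 0.25, and positively correlated later utilities add to it. *b* then exceeds 0.25 and the error changes sign instead of disappearing.

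**5. Withdrawal between allocation and baseline.** The article gives no rate. As illustration, one or two such families are 10-20% of an initial A or B arm in one cohort (1/10, 2/10), 5-10% of group C in one cohort (1/20, 2/20), and 2.5-5% of a final group (1/40, 2/40).

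**6. Group C.** Each final inpatient group has 2 × 10 = 20 participants from the first randomisation and 2 × 10 = 20 from group C. Half of the A-versus-B comparison therefore needs a second baseline. The natural candidate is the month-12 visit, which is also the end of usual care. The text does not say so, nor whether that visit comes before A or B is disclosed.

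**The case against.** - **The article is condensed.** The exact order of visit, draw and disclosure is detail that a full protocol may hold, and the participant flow chart is not reproduced in the text reviewed. This stands as a reason for caution about the disclosure date. It does not remove the point, because the article does fix baseline, and fixes it at treatment start.
- **The primary outcome is largely unaffected.** Height is averaged over three stadiometer readings and weight is taken on a calibrated scale. This stands: the reporting concern applies to EQ-5D, a secondary outcome.
- **Nobody is removed from the intention-to-treat analysis.** A reader might infer that families who withdraw on hearing their allocation have no baseline at all and so drop out of that analysis. The article does not support this. Screening yields an SDS-BMI before randomisation, baseline is not a listed GEE covariate, and missing economic data are imputed. Someone who attends no visit contributes nothing to the GEE, but an earlier baseline would not supply the missing follow-up outcomes either.
- **Arm-dependent refusal is not documented.** A reader might take the Discussion's remark that "an inpatient period of 2 or 6 months imposes a very heavy burden on families and children" as evidence of it. That remark explains expected recruitment problems, before randomisation, and treats both durations together. Families unwilling to take part in treatment are already excluded.
- **The shift is assumed.** This stands. Moreover, a lasting change in wellbeing after allocation would be part of the treatment effect; only a transient reaction is bias.
- **Group C's second draw is described as following the usual-care year.** This makes disclosure before the month-12 visit less likely, but the order is not stated.

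**Conclusion.** The point holds for the self-reported baseline. Baseline is placed after an unblinded randomisation for groups A and B, so the baseline EQ-5D can be influenced by the allocation. It carries 0.25 year of weight in the QALY; a transient arm difference of 0.02 to 0.10 would shift the QALY difference by 0.005 to 0.025. The weight follows from the article, whereas the range is an assumption and its direction is unknown.

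Withdrawal before treatment start costs the planned EQ-5D. It does not cost the screening SDS-BMI or, by itself, a place in the GEE. The article does not say whether the screening SDS-BMI may serve as baseline. For group C the definition has two readings, and half of each final inpatient group comes through group C.

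This should be corrected because the remedy is cheap. It does not call the primary SDS-BMI comparison into question.

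**What to change.** Replace the definition of baseline with text to this effect:

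> Baseline EQ-5D, height and weight are measured after informed consent and before the allocation is drawn or disclosed. The SDS-BMI from this measurement is the baseline value. For group C, the first baseline is this same measurement, and the second is the month-12 visit, completed before allocation to A or B is disclosed.

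These measures could be taken at the eligibility screening, provided consent has been obtained. Fasting bloods and the glucose tolerance test may stay at treatment start. SDS-BMI can be repeated then as a secondary value.

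Data collection began in August 2009, so participants already enrolled cannot be given a new baseline. For them, report when baseline was taken relative to disclosure and, by arm, how many were randomised but never started.

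The cost is the re-ordering of three simple measurements and a few sentences of text. The small downside is a short interval between baseline and the first treatment day, which should be recorded.

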### Height, weight and circumferences

Height is recorded with a Holtain stadiometer fixed on the wall with an accuracy of 1 mm. The stadiometer is calibrated before every first measurement. Height is recorded three times of which the average is calculated. Weight is measured in light clothing without shoes and recorded with a calibrated SECA digital weight chair that has a limit of 230 kg and an accuracy of 0.005 kg.

Weight and height are used to calculate BMI (weight in kilograms divided by the square of height in meters). The degree of overweight is quantified using Cole's least mean square method, which normalizes the BMI's skewed distribution and expresses BMI as SDS-BMI [19]. These calculations are performed using (http://www.growthanalyser.org; version 3.5, program by "Stichting Kind en Groei", downloaded in July 2010). The data from the fourth Dutch growth study among children of 1997 are used as reference. The SDS-BMI indicates how many standard deviations a measurement is above or below the median of the distribution. Circumferences of the neck, waist, abdomen (WHO as well as maximum) and hip are measured with a tape measure. The participant has to stand up straight (in underwear) with the arms alongside the body and the feet in resting position. The circumferences are measured with an accuracy of 1 mm.

### Blood pressure

Blood pressure is measured with a digital blood pressure monitor (Heine, type Gamma E60). A cuff size with a width of two-third of the upper arm length is used that completely covers the arm circumference. For most participants a 17 cm cuff size (CAO2, arm circumference 33-41 cm) is used. If necessary, a 14 cm cuff size (CAO1, arm circumference 22 32 cm) is used. Blood pressure is measured in sitting position after sitting still for at least 5 minutes. Blood pressure is measured three times. For the analyses, the averages of the three systolic blood pressure and diastolic blood pressure readings are used.

### Bio-electrical impedance spectroscopy

Bio-electrical impedance spectroscopy (BIS) measurements are conducted with a Body Impedance Analyzer BIA 101/s (Akern-SRL Systems by EQUIP Medikey BV). Two current electrodes (tetra-polar electrodes (3 M red Dot AG/AgCl)) are placed at the dorsal surfaces of the hand and foot on the distal portion of the second metacarpal and metatarsal, respectively. Two detector electrodes are placed at the posterior wrist between the styloid processes of the radius and ulna and at the anterior ankle between the tibial and fibular malleoli. The resistance (Ohm) is used in the analysis to determine fat mass (FM) and fat free mass (FFM). The equation used for the children and adolescents in this study for percentage body fat (%BF) is the adjusted Kushner equation {Wt-[0.59(Ht2/R)+0.065(Wt)+0.04]/[0.754(Wt)]} x 100 [20]. This equation is adjusted and validated by Newton et al [21].

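### The body-fat equation as printed cannot return a percentage: it gives about 100 times body weight and should be restored from its cited sources

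*Protocol article*

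**What the plan says.** The section Bio-electrical impedance spectroscopy states: "The resistance (Ohm) is used in the analysis to determine fat mass (FM) and fat free mass (FFM"). It then gives the equation "for percentage body fat (%BF") as "Wt-[0.59(Ht2/R)+0.065(Wt)+0.04]/[0.754(Wt)]} x 100", preceded by an opening brace, and cites one source for the equation and one for its adjustment and validation. Ohm is named for resistance. The equation itself carries no units for height or weight.

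The Discussion explains the choice. The original equation "is developed to calculate total body water and is therefore not applicable", so an adjusted form is used. Equations made for obese children would suit better, but the authors are restricted because resistance is the only impedance quantity recorded. The article gives no other form of the equation and no worked value.

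**The concern.** A percentage must lie between 0 and 100. In the printed grouping the slash applies only to the square-bracketed term, and the leading Wt stands undivided inside the braces. A dimensionless ratio is therefore taken from a weight in kilograms, and the difference is multiplied by 100.

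This is a derivation rule in the Methods, not background text. Code written from it would return values close to 100 × Wt, and a comparison of such values would in effect compare body weights. There is also a less visible risk. Someone who notices the absurd value and simply moves the closing brace gets numbers that mostly lie between 0 and 100 and can pass a range check, although that regrouping may not be the intended equation.

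**Working it through.** **Inputs.** The coefficients 0.59, 0.065, 0.04 and 0.754 are those printed. The article reports no participant weights, heights or resistances, so these are assumed. Weight is in kg (the section Height, weight and circumferences describes a "SECA digital weight chair that has a limit of 230 kg and an accuracy of 0.005 kg"), resistance in ohm, and height in cm, since the equation does not state its unit. There is no printed body-fat value to reproduce.

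**Definitions.** Let W = 0.59(Ht²/R) + 0.065(Wt) + 0.04. Three groupings are compared:

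- Printed: {Wt − W/(0.754 Wt)} × 100
- Regrouped: {Wt − W/0.754}/Wt × 100, which equals {1 − W/(0.754 Wt)} × 100
- Brace moved: {Wt − W}/(0.754 Wt) × 100

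**Case 1: 100 kg, 165 cm, 500 ohm.** W = 0.59 × 27,225/500 + 6.5 + 0.04 = 32.13 + 6.54 = 38.67. Also 0.754 × 100 = 75.4, and 38.67/75.4 = 0.513.

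- Printed: (100 − 0.513) × 100 = 9,949%
- Regrouped: (1 − 0.513) × 100 = 48.7%
- Brace moved: (100 − 38.67)/75.4 × 100 = 81.3%

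**Case 2: 60 kg, 145 cm, 600 ohm.** W = 0.59 × 21,025/600 + 3.9 + 0.04 = 20.67 + 3.94 = 24.61. Also 0.754 × 60 = 45.24, and 24.61/45.24 = 0.544.

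- Printed: (60 − 0.544) × 100 = 5,946%
- Regrouped: (1 − 0.544) × 100 = 45.6%
- Brace moved: (60 − 24.61)/45.24 × 100 = 78.2%

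**Sensitivity to the assumed inputs.** The three groupings were evaluated at 24 combinations of weight 40 to 230 kg, height 135 to 185 cm and resistance 250 to 750 ohm:

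| Grouping | Lowest | Highest |
|---|---|---|
| Printed | 3,919.9% | 22,968.1% |
| Regrouped | 19.9% | 68.1% |
| Brace moved | 52.6% | 100.7% |

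The subtracted fraction was below 1 throughout, so the printed form always lay between 100(Wt − 1) and 100 Wt. At 100 kg and 165 cm, changing resistance from 380 to 630 ohm moved it only from 9,935.3% to 9,957.5%. Reading height in metres does not rescue it: 100 kg, 1.65 m and 480 ohm give about 9,991%.

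**Difference between the two regroupings.** Brace moved minus regrouped is (1/0.754 − 1) × 100 = (1.326 − 1) × 100 = 32.6 percentage points. It does not depend on height, weight or resistance. If the regrouped form is the intended one, this offset cancels from changes and group differences in percentage fat. It does not cancel from fat mass in kg: if fat mass is taken as the percentage times weight, the excess is 0.326 × Wt, and a 10 kg weight loss would add about 3.3 kg of spurious fat loss.

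**The case against.** The strongest objection is that the error reveals itself. No analyst would accept a body-fat value of several thousand percent, and the article cites sources from which the equation can be checked. A misprint is the likeliest explanation. This stands. A reader might infer that every body-composition result of the trial is wrong, but that holds only if the printed form was coded, and the article gives no evidence that it was.

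The variable is also peripheral. The section Measurements names SDS-BMI as the primary outcome, and quality of life and cardiovascular risk factors as secondary. The list of risk factors is given by example and does not include percentage fat, fat mass or fat-free mass. The sample size rests on SDS-BMI, and the economic ratios on SDS-BMI and QALYs. This also stands, so a reading that the main conclusions are at risk is not supported.

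A reader might further take the printed equation as the stated rule for fat mass and fat-free mass. The text says that resistance serves to determine them and gives this equation for percentage fat. Deriving the two masses from the percentage is natural, but it is not stated.

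The replacement cannot be read off the article with certainty. The Discussion supports reading W as total body water, but nothing says what 0.754 represents. The moved-brace form is equally dimensionless, so the case against it rests on plausibility under assumed inputs, not on dimensions. The structure therefore needs checking as well as the coefficients.

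Finally, the flattened superscript in Ht2 raises the possibility that a fraction layout was lost when the text was read from PDF. The braces, brackets and slash are explicit characters, so this is unlikely.

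**Conclusion.** The equation is wrong as written. It returns about 100 × Wt: 9,949% and 5,946% in the two worked cases, and above 10,000% for participants heavier than about 100 kg. The exact figures depend on assumed weights, heights and resistances, but the conclusion does not, because the subtracted fraction is below 1 for any plausible input.

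The consequence is limited: a printed Methods rule needs correcting, with harm to body-composition results only if the code repeats it. The regrouped form, with 48.7% and 45.6% in the two cases, is the one consistent with W being total body water, provided that 0.754 is the water fraction of fat-free mass. That second premise is an inference.

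**What to change.** Restore the equation from the two cited sources, checking both the placement of the brackets and the coefficients. State the units of Ht, R and Wt beside it. Check that the analysis code matches the restored form, and say how fat mass and fat-free mass are obtained.

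Subject to that check, the candidate is %BF = {Wt − [0.59(Ht²/R) + 0.065(Wt) + 0.04]/0.754}/Wt × 100. Moving the brace to divide Wt − W by 0.754(Wt) should not be adopted as the repair unless the sources confirm it.

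The cost is a one-line correction and a short code review. No new data are needed, because the correction uses the same weight, height and resistance measurements.
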